#### Secondary outcome measures

ANCOVA models will be also used for continuous variables, including the initial S-STS score as a covariate. The number of days with a patient-rated S-STS score of 0 will be calculated for each patient, and compared between the groups. Because this outcome measure is a count variable, Poisson regression will be applied. Cumulative regression models will be applied for the comparison between groups for the BIS, CGI and the C-SSRS-items concerning severity and intensity of ideation. For the analysis of longitudinal data, (i.e. the modelling of weekly score change), mixed regression models will be used.

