### Methods/Design

The present study is a multi-center, 4 year, randomized placebo-controlled double-blind trial. Patients with unipolar or bipolar disorder suffering from a major depressive episode with suicidal thoughts and/or behavior according to DSM IV criteria will be randomly allocated to lithium therapy plus treatment as usual versus placebo treatment plus treatment as usual. The hypothesis to be tested is that lithium treatment plus treatment as usual leads to a significant reduction of suicidal thoughts and/or behavior compared to placebo therapy plus treatment as usual within 5 weeks of treatment. The primary end point of this study is the change in Sheehan Suicidality Tracking Scale (S-STS, [17]) between the beginning of treatment and after a treatment episode of 5 weeks. Further endpoint in this study are changes in the Columbia-Suicide Severity Rating Scale (C-SSRS, [18]), the Montgomery Asberg Depression Rating Scale (MADRS, [19]), the Hamilton Anxiety Scale (HAM-A, [20]), the Clinical Global Impression Scale (CGI, [21]) and the Barratt Impulsivity Scale (BIS, [22]) from initial treatment to 5 weeks post treatment. A comparison of total scores in the C-SSRS, MADRS, HAM-A and the Young Mania Rating Scale (YMRS, [23]) within the participating centers will be conducted. In addition, the number and dosage of concurrent medication and number of psychotherapy hours will be explored as secondary endpoint. Weekly changes in the C-SSRS, MADRS, HAM-A and YMRS within the observation period and percentage of days where the S-STS Scale score equals zero will be reported. Two-hundred and fifty-four patients will be included with, thereof 127 in each treatment group. Recruitment started on October first, 2013 and will end on September 30^th^, 2017. Treatment includes 5 weeks of treatment plus 1 week of follow-up. For a detailed description of the inclusion and exclusion criteria, please see Table 1.

**Table 1 Tab1:** In-and exclusion criteria

Inclusion criteria	Exclusion criteria

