#### Patient administered scales

To investigate whether the psychological construct of impulsivity is associated with suicidality, the Barratt Impulsiveness Scale (BIS) will be applied at weekly intervals during the study. The BIS is a widely used measure of impulsiveness and includes 30 items that are scored to yield six first-order factors (attention, motor, self-control, cognitive complexity, perseverance and cognitive instability impulsiveness) and three second-order factors (attentional, motor, and non-planning impulsiveness). The patients will be also asked to fill out the S-STS as a self-rating instrument on a daily basis.

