### Power analysis and sample size calculation

A comparable study published by Khan et al. [26] of a 6-week double-blind trial in 40 patients found a score reduction of 4.8 (SD = 5.1) in the clinician administered S-STS in the placebo group, while a score reduction of 6.7 (SD = 5.8) was found among the lithium group The assumption that all lithium patients achieve a therapeutic serum-level in the current study seems to be reasonable due to the considerable higher lithium dose in comparison with the Khan et al. study. Therefore, these values have been used as estimates for the expected group difference in this study.

With an alpha level of 0.05, and statistical power of 0.8, sample size estimation for a two-sided *t*-test with unequal variances results in a required number of 131 patients per group. Nevertheless, a *t*-test has considerably less power than an analysis of covariance (ANCOVA), which will be used in this analysis. Borm et al. [27] showed for sample size n and a baseline-follow-up correlation rho, that an ANCOVA with (1-rho^2)*n subjects has the same power as the corresponding *t*-test. There is no published data on test-retest correlations of the S-STS to our knowledge; however, a recalculation of data from the “Basis-Studie Kompetenznetz Depression” [28] with 1014 naturalistically treated depressed patients showed correlations from 0.36 to 0.54 for the self-report S-STS between baseline and week 8. Therefore, a conservative assumption of 0.3 for the expected correlation was chosen, which yields a number of 120 patients per group. These patients will form the modified Intention to Treat (ITT) sample including all patients who will be randomized and not discontinue from the study before any efficacy measurement. A rate of approximately 5 % of randomized patients dropping out for any reason before entering the ITT sample is presumed, which results in 127 patients needed to be randomized per group. Therefore, 508 patients will be required to be screened assuming a rate of 50 % of screened patients fulfilling the inclusion criteria. We are expecting good adherence to the intervention as this will not result in major side effects. However, we anticipate that there will be about 5 % loss to follow-up, and this is accounted for in the sample size estimation.

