### Statistical analysis

Descriptive statistics using proportions, means and standard deviations will be reported where appropriate. All efficacy outcome measures will be analyzed on an intent-to-treat (last observation carried forward) basis and study completer basis. Results will be presented with 95 % confidence intervals where applicable. Proportions of adverse events will be summarized. All statistical tests will be two-sided using an alpha level of 0.05. Analyses will be adjusted for age and gender when there is a significant difference between the groups at baseline.

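### Poisson regression for the count of zero-score days probably gives intervals that are too narrow, and the article leaves open whether the outcome is a number or a percentage of days

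*Protocol article*

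**What the plan says.** Under Patient administered scales, patients are asked to "fill out the S-STS as a self-rating instrument on a daily basis". Methods/Design sets the period: "Treatment includes 5 weeks of treatment plus 1 week of follow-up". Secondary outcome measures reduces these ratings to one figure per patient: "The number of days with a patient-rated S-STS score of 0 will be calculated for each patient, and compared between the groups". It then names the model and its only reason: "Because this outcome measure is a count variable, Poisson regression will be applied". Methods/Design lists the same quantity differently: "percentage of days where the S-STS Scale score equals zero will be reported". Statistical analysis adds a general rule on missing data: "All efficacy outcome measures will be analyzed on an intent-to-treat (last observation carried forward) basis and study completer basis".

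**The concern.** Poisson regression takes each patient's count to have a variance equal to its mean. This outcome differs in two ways. It cannot exceed the number of days rated, which by itself pushes the variance below the mean. And a patient free of suicidal thoughts on one day is likely to be free of them on the next, which pushes the variance up, usually by much more. If the second effect dominates, the Poisson standard error is too small, the 95% interval covers less than 95%, and the test rejects too often.

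A second matter is separate. A raw number of days also depends on how many days a patient rated. If the arms differ in diary completion or drop-out, the comparison of raw numbers shifts for reasons unrelated to suicidality. A percentage of rated days does not have that dependence, and the article uses both descriptions.

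**Working it through.** The article states no variance, power or sample size for this outcome, so there is no figure of its own to reproduce. Its primary-endpoint numbers do reproduce: a t-test with unequal variances for a difference of 6.7 − 4.8 = 1.9 needs 131 per group; 131 × (1 − 0.3²) = 119.2, so 120; 120 / 0.95 = 126.3, so 127. They have no bearing here beyond supplying 120 per group for the simulation.

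**Inputs**
- Days per patient: 5 weeks × 7 = 35 (Methods/Design). The follow-up week is left out, as an assumption.
- Two-sided 5% level (Statistical analysis).
- Share of zero days, p: not given. Assumed 0.2 to 0.8.
- Within-patient correlation of the daily zero/non-zero indicator, rho: not given. The only related figure is in the sample size section, where data from another study "showed correlations from 0.36 to 0.54 for the self-report S-STS between baseline and week 8". That is a correlation of scores eight weeks apart. Neighbouring days should correlate more, while cutting a score into zero or not tends to lower a correlation. So 0.36 to 0.54 is only a stand-in, and 0.1 is shown as a low case.

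**Formulas.** With beta-binomial counts over 35 days, the mean is 35p and the variance is 35p(1 − p)(1 + 34·rho). Hence:
- variance/mean = (1 − p)(1 + 34·rho), which Poisson sets to 1;
- true SE / Poisson SE of the log rate ratio = square root of that ratio;
- type I error of the nominal 5% test ≈ 2 × [1 − Φ(1.96 / SE factor)].

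Example, p = 0.2 and rho = 0.36: 0.8 × (1 + 12.24) = 10.59; √10.59 = 3.25; 1.96 / 3.25 = 0.60, giving about 55%.

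| p | rho | variance/mean | SE factor | simulated type I error |
|---|---|---|---|---|
| 0.2 | 0.36 | 10.59 | 3.25 | 54.5% |
| 0.2 | 0.54 | 15.49 | 3.94 | 62.2% |
| 0.5 | 0.36 | 6.62 | 2.57 | 45.5% |
| 0.5 | 0.54 | 9.68 | 3.11 | 52.6% |
| 0.8 | 0.36 | 2.65 | 1.63 | 21.9% |
| 0.8 | 0.54 | 3.87 | 1.97 | 31.5% |
| 0.2 | 0.1 | 3.52 | 1.88 | 30.8% |
| 0.5 | 0.1 | 2.20 | 1.48 | 17.9% |
| 0.8 | 0.1 | 0.88 | 0.94 | 3.8% |

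The variance exceeds the mean once rho > p / [34(1 − p)]: above 0.007 at p = 0.2, 0.029 at p = 0.5 and 0.118 at p = 0.8. Little correlation is needed unless most days are zero days.

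**Check on the model.** The formula assumes a constant zero-day share over the five weeks. A second simulation let the share rise over time, with a patient effect and serial correlation between days. Mean counts ran from 4.5 to 17.5 of 35 days. The SE factor was 1.4 to 3.1 and type I error 13% to 52%.

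**Check on the remedy.** An empirical (robust) variance on the same beta-binomial counts gave type I error of about 4% to 6%.

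**Number against percentage.** Suppose both arms have the same daily chance of a zero score, but mean rated days are 35 in one and 30 in the other (assumed). The ratio of raw counts is then 30 / 35 = 0.86 with no treatment effect. With 33 against 31 it is 31 / 33 = 0.94. A ratio based on rated days would be 1 in both cases.

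**The case against.** The best defence has four parts.

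- **One row per patient.** A reader might infer that daily ratings enter the model as independent observations. The article does not support that: it forms one count per patient. The correlation between days shows up only as extra variance between patients. This part stands, and the point is overdispersion, not a unit-of-analysis error.
- **The size rests on assumptions.** A reader might conclude that the intervals are certainly several times too narrow. The article supplies neither p nor rho, and the factor falls to 0.94 at p = 0.8 and rho = 0.1. This stands too, so only a conditional range can be given. The eligibility table requires a score of at least 8 at entry, and the assumed mean reductions are 4.8 and 6.7. That hints at a modest share of zero days over the whole period, but does not establish it.
- **An offset, a dispersion term or robust errors may be in the full protocol or SAP.** Their absence from a condensed article is no finding, and Poisson regression can carry all of them. What remains is that the article chooses the model on a reason that does not support it, and a plan that followed the sentence as written would inherit the problem.
- **LOCF or the completer set may even out the days.** Possibly, but the article does not say whether LOCF applies to the diaries. If it does, a leaver's remaining days all copy one rating, which levels the denominators but adds to the overdispersion.

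On the endpoint, one section reports a percentage and the other tests a number. A Poisson model with rated days as offset would fit both. They are not necessarily competing endpoints, but the wording has to be aligned.

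**Conclusion.** The point holds as a conditional one. Plain Poisson regression is probably the wrong variance model for this outcome. The true standard error is about 1.6 to 4 times the Poisson standard error for p of 0.2 to 0.8 and rho of 0.36 to 0.54, with type I error of about 22% to 62% at a nominal 5%. Both inputs are assumptions. At low correlation with a high share of zero days there is no narrowing.

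The mismatch between a number and a percentage of days is real but can be reconciled. Its effect is bias when rated days differ between arms. A reader might add it to the reasons for narrow intervals, but the comparison of 35 with 30 days shows a shifted ratio, not an understated standard error.

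Severity is moderate. This is one of several secondary outcomes, and neither the primary ANCOVA nor the sample size depends on it.

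**What to change.** State the endpoint once, in the same words in Methods/Design and Secondary outcome measures: days with a self-rated S-STS of 0 out of days rated. Analyse it with a quasi-binomial or beta-binomial model with treatment group as factor. If a count model is kept, use log(rated days) as offset together with robust standard errors. Say whether LOCF applies to the daily ratings. If the SAP already contains these elements, aligning the two descriptions is enough.

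The cost is about one sentence and no new data. The interval will usually be wider than the plain Poisson one. If the data turn out to vary less than Poisson implies, it would be narrower.

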### Data and safety management

Pre-trial visits will be performed at all sites by the coordination Centre of Clinical Trials (KKS) Dresden to evaluate the qualification of the sites, and the recruitment of the necessary number of patients. To ensure the study is conducted in accordance with the protocol and Good Clinical Practice (GCP), monitoring will be performed by experienced personnel from the KKS Dresden at each site in appointed time intervals (per site, once at initiation of the study, once after the first subject was randomized, once when the last subject completed the study), for a total of 11 regular monitoring visits per site. The monitoring process will be performed according to the SOPs of the sponsor of this trial, the Dresden University of Technology. The monitor will check completeness and plausibility of the data and will align the study data to the original data (Source Data Verification). This will be accomplished by accessing the subject’s charts. As part of the consent, subjects give permission for study personnel to access their medical charts. The monitor will ensure the basic claim of integrity and protection of the subject’s privacy. All trials with the Dresden University of Technology will be audited. All assessed data will be recorded in the eCRFs with an audit trail by authorized personnel. A list of signs and identification codes of all personnel that will enter data into the CRFs will be stored in the Trial Master File. Corrections are only allowed to be processed by these persons. All study data will be stored for 10 years and will be destroyed afterwards.

This trial will be supervised by a scientific advisory board including members experienced in assuring data quality and safety (DSMB). These members have supervised the development of this protocol and will supervise the progress of the trial, including decision making on whether to perform interim analyses or modify/stop the trial in case of unforeseeable problems. The members of this board are completely independent of the coordinating investigators and the medical institution involved. As per protocol, all serious adverse events and reactions will be documented by the investigators, and due to German Drug law, evaluated and sent to the sponsor, or if necessary to the regulatory authority.

### Ethical considerations

An extensive number of patients with depression have suicidal thoughts and/or behavior during their acute episodes of illness. All patients will receive TAU. Because of the long history of lithium in the treatment of mood disorders with well-known (side) effects, the risks associated with lithium treatment in the proposed study protocol are considered low, especially as this is only a 5-week trial. The potential benefits of this trial clearly outweigh the potential risks associated with lithium treatment. Finally, it has been shown that patients at high risk for suicide can safely be included in clinical trials such as this one if proper precautions are followed. In addition, these patients need to be included to enable premarket assessments of the risks and benefits of medications related to suicidal ideation, suicidal behavior, and suicide in this population [29].

The study has been approved by the Ethics Committee in Dresden (coordinating centre) on August, 23th 2013 (EUDRACT number 2013-000970–31) and was also approved for all participating centres (Dresden University Clinic, Dresden Neustadt, Berlin, Bochum, Frankfurt, Göttingen).

## Discussion

Lithium has shown to have suicide-preventing effects in patients with affective disorders over the long-term course. No study has investigated whether this effect occurs at the beginning of treatment or develops after months of ongoing lithium therapy. The results of this study should indicate whether lithium leads to a decrease in suicidal thoughts and/or behavior within the beginning of the treatment (5 weeks).

There is a critical need to identify treatments that will acutely decrease suicidal ideation and/or behavior. Lithium therapy is widely available and inexpensive. The potential benefits of lithium therapy on acute suicidal ideation and/or behavior in patients with affective disorders need to be clarified.

In designing this study, we aimed to be as close as possible to a real-world clinical setting. The recruiting centers are a mix of university and community based psychiatric hospitals which represents a broad spectrum of patients with affective disorders. We are aware that the TAU condition may cause additional heterogeneity, as this can vary from center to center, or even within one center through different approaches of the treating psychiatrists.

This proposed study has several limitations: i) suicidal patients are generally excluded from clinical (especially pharmacological) trials. Therefore special attention and care is needed to minimize the risk in this high-risk population while undergoing a clinical trial. ii) Patients with acute suicidal crisis admitted to the hospital and treated with combined pharmacological and psychological treatments sometimes show a sudden improvement in terms of their suicidality, especially in those who were intoxicated at the time of admission. In the literature this effect is well-described as a suicide-cathartic effect after a suicide attempt [30]). Suicidality fluctuates in patients with depressive symptoms from the day of admission to a few days later when they usually are being informed about the study. As Davis et al. [31] stated, interpersonal support (attention from loved ones, and benefits from therapy) may be a mechanism by which a patient experiences immediate relief, and therefore decreased suicidal ideation/behavior. iii) Currently, no approved medication exists to treat suicidality. Patients may express concerns that they will be receiving a medication that is not approved for their specific symptoms and may refuse to participate.

Despite these challenges we anticipate that the results of this study (coming from a real world setting), will provide novel information that could lead to better pharmacological treatment and prevention strategies for patients with an acute major depressive episode with suicidal ideation and/or behavior, and may help reduce the immense individual distress for families in which a member is suffering from depression with suicidality.
